## Abstract

**Background:**

Essential strategies are needed to help reduce the number of post-operative complications and associated costs for breast cancer patients undergoing reconstructive breast surgery. Evidence suggests that local heat preconditioning could help improve the provision of this procedure by reducing skin necrosis. Before testing the effectiveness of heat preconditioning in a definitive randomised controlled trial (RCT), we must first establish the best way to measure skin necrosis and estimate the event rate using this definition.

**Methods:**

PREHEAT is a single-blind randomised controlled feasibility trial comparing local heat preconditioning, using a hot water bottle, against standard care on skin necrosis among breast cancer patients undergoing reconstructive breast surgery. The primary objective of this study is to determine the best way to measure skin necrosis and to estimate the event rate using this definition in each trial arm. Secondary feasibility objectives include estimating recruitment and 30 day follow-up retention rates, levels of compliance with the heating protocol, length of stay in hospital and the rates of surgical versus conservative management of skin necrosis. The information from these objectives will inform the design of a larger definitive effectiveness and cost-effectiveness RCT.

**Discussion:**

This article describes the PREHEAT trial protocol and detailed statistical analysis plan, which includes the pre-specified criteria and process for establishing the best way to measure necrosis. This study will provide the evidence needed to establish the best way to measure skin necrosis, to use as the primary outcome in a future RCT to definitively test the effectiveness of local heat preconditioning. The pre-specified statistical analysis plan, developed prior to unblinded data extraction, sets out the analysis strategy and a comparative framework to support a committee evaluation of skin necrosis measurements. It will increase the transparency of the data analysis for the PREHEAT trial.

**Trial registration:**

ISRCTN ISRCTN15744669. Registered 25 February 2015

**Electronic supplementary material:**

The online version of this article (10.1186/s40814-017-0223-y) contains supplementary material, which is available to authorized users.

## Background

Although the majority of women with breast cancer are treated with breast conserving surgery, approximately 30% will still need a mastectomy. The 2002 National Institute for Clinical Excellence (NICE) guidelines recommend immediate breast reconstruction whenever it is safe [1]. Revised NICE guidance in 2009 re-emphasises the importance of immediate reconstruction after mastectomy [2].

There are essentially two types of reconstruction that a patient can have after mastectomy: implant-based or autologous flaps, where the patient’s own tissue is used to create a new breast. Skin-sparing mastectomy (SSM) followed by autologous microsurgical breast reconstruction is an increasingly popular procedure within the UK [3]. It results in highly satisfactory results both oncologically and cosmetically from a surgical and patient’s perspective [4]. In 2011, 16,485 women underwent mastectomy in the UK and approximately a third of these underwent autologous reconstruction [5].

These procedures, particularly autologous reconstruction, are highly labour intensive requiring significant expertise and involvement of several healthcare professionals. Implant-based reconstruction is less expensive initially than autologous reconstruction but more patients are opting for the latter due to more satisfactory results [6]. A bilateral mastectomy and reconstruction can take an entire day of operating theatre time. The average cost of a free flap breast reconstruction is estimated at £10,910 compared to an implant only reconstruction, which costs £8034 [6]. However, it is important to remember that autologous reconstruction has a lower long-term cost to the NHS as it requires fewer revisions and has higher patient satisfaction compared to implant reconstruction [7].

According to the NHS’ Institute for Innovation and Improvement, reducing the length of hospital stay is ranked as a level 1 priority [8]. In autologous breast surgery, the average length of stay (LOS) following a “deep inferior epigastric perforator” (DIEP) flap is 8 days and our own LOS concurs. In the USA, the LOS is much shorter however this is mainly due to the reluctant nature of private funding from insurance companies for the same procedure [9]. LOS is the most influential factor in reducing the cost of autologous breast reconstruction [9]. Local heat preconditioning could help improve the provision of this procedure by helping to reduce the complications and overall costs associated with its service delivery.

### Evidence for local heat precondition

A non-randomised phase 1 study conducted by three of the authors ([name]) in 50 participants looked at the use of heat preconditioning to reduce skin necrosis in SSM. The study showed a reduction in necrosis from 36 to 12% (controls vs tests) and an average length of stay from 8 to 4 days [10]. There is little data on the cost implications of specifically skin necrosis, however, the incidence rate is between 20 and 40% and the cost of surgical treatment (debridement and skin graft) is approximately £1782 plus extra theatre time (£3840 for half a day in theatre [11]). Extra hospital stay means the costs can spiral into the thousands.

The simple heat preconditioning intervention we are exploring has the potential to improve wound healing preoperatively and to prevent complications in a safe way reducing the burden to patients at minimal cost. This is important in a modern NHS with increasing financial constraints and, if found to be efficacious, heat preconditioning could allow us to offer autologous reconstruction to more patients. Aside from the financial benefits, benefits to patients would be improved wound healing resulting in quicker recovery and reduced LOS with faster progression to adjuvant therapy. This means a quicker return to normal life but more importantly, earlier discharge improves recovery, reduces the risks of hospital-acquired infections and venous thromboembolism [8].

### Study aim

PREHEAT is a feasibility study for a trial that will evaluate local heat preconditioning with respect to its effects on wound healing after reconstructive breast surgery in patients with breast cancer. The aim of this study is to inform the design of a larger trial among breast cancer patients undergoing SSM and nipple-sparing mastectomy (NSM) focusing on effectiveness. This article describes the PREHEAT trial protocol (version 1.1, 26/02/2016) and the detailed statistical analysis plan, which has been developed prior to unblinded data extraction to meet the trials objectives. The protocol was prepared in accordance with the Standard Protocol Items: Recommendations for Interventional Trials (SPIRIT) guidance [12]. The trial SPIRIT checklist can be viewed in Additional file 1.

### Objectives

#### Primary objective

The primary objective of PREHEAT is to identify the best way to measure a skin necrosis and to estimate the necrosis event rate in the treatment and control arm using this definition.

#### Secondary objectives

Secondary objectives are the following:i.To estimate the recruitment rateii.To estimate 30-day follow-up retentioniii.To assess the level of adherence with the heating protocoliv.To estimate the effect of heat preconditioning on length of hospital stayv.To estimate the rates of surgical versus conservative management of skin necrosis

The information gathered from this study will be used to inform the design of a large multicenter effectiveness and cost effectiveness trial.

## Methods/design

PREHEAT is a randomised two-arm single-blind parallel group controlled trial of local heat preconditioning in breast cancer patients undergoing SSM and NSM. The comparator intervention is mastectomy only without any heat preconditioning. Surgeons and assessors evaluating necrosis outcome will be blind to treatment allocation. The aim is to recruit approximately 180 patients over a fixed 2-year recruitment period.

### Study population

The study population will be women over the age of 18 (no maximum age limit) undergoing SSM or NSM mastectomy and immediate breast reconstruction (autologous and implant). This will include diabetics, smokers and BRCA carrier prophylactic mastectomies with immediate breast reconstruction. Exclusion criteria include delayed (2-stage) reconstruction patients, patients with a latex allergy and patients with inflammatory cancer.

### Intervention

The intervention is heat preconditioning of the breast (to be operated on) the night prior to the surgery by means of a hot water bottle. Participants in the intervention arm will be given a hot water bottle and an underwater thermometer for use at home. The preconditioning heating protocol is as follows: the participants will need to heat water in a saucepan at home to 43 °C and pour it into the bottle. This is then placed on the naked study breast (the breast to be operated on) over the nipple-areola complex for 30 min. The breast is then allowed to cool for 30 min to body temperature. The participants will then need to do another 30-min application of heat at the same temperature for 30 min with fresh heated water. The bottle must be placed in the same area. After another 30-min break, the participants will need to do a final, third heat application. The preconditioning intervention will be undertaken once, 12 h before surgery, i.e. the evening before. For the BRCA carrier status participant undergoing bilateral mastectomy and reconstruction, we will ask them to heat only the right breast.

This heating procedure is based on the protocol used in our phase 1 study and an experimental animal model investigating the effect of local heat preconditioning [10, 13]. A temperature of 43 °C provides heat application to a supraphysiological level without causing a burn. We will ask participants to record the temperature of the water and the number of heating applications they undertook to assess adherence to the heating protocol. All usual medication will be continued.

### Randomisation and blinding

Participants will be allocated to treatment arm via an online randomisation system hosted by the King’s College London Clinical Trials Unit (KCTU) to ensure concealment of treatment allocation for clinicians who are assessing participants. Randomisation is undertaken with equal allocation to each arm (1:1) using minimisation stratifying for the following:Type of reconstruction (Implant vs Autologous)Smoking status (yes/no)Diabetic (yes/no)BRCA carrier status (yes/no)

Surgeons and outcome assessors will be blind to treatment allocation.

### Outcomes

#### Primary outcome

Necrosis will be measured in three different ways as follows:Necrosis (yes/no): by clinical judgementNecrosis depth (assessed using the SKIN score as described below): recorded independently by two clinical outcome assessors and from photographs by two further assessors.Necrosis area (mm^2^): recorded by depth using a transparent grid on day of occurrence independently by two clinical outcome assessor when necrosis is present.

Necrosis depth was initially recorded as none/superficial/partial/full/superficial + partial/full thickness during the first part of the PREHEAT study (for patients 1 to 34). Following publication of a validated SKIN score by Lemaine et al. 2015 [14], a protocol update was made in February 2016 and the SKIN score replaced the original recorded categories. The SKIN score classifies the depth of necrosis from A to D where A is none; B is colour change of flap suggesting impaired perfusion or ischaemic injury; C is partial thickness skin flap necrosis resulting in breakdown of the wound; D is full thickness skin flap necrosis [14]. All outcome assessors will be provided with training in the assessment protocol, which uses previously published and accepted methods of measuring wound area.

#### Secondary outcomes

Secondary outcomes include:Recruitment rate30 day follow-up retention proportionLevel of adherence with heating protocolLength of stay in hospitalRates of surgical/conservative management of skin necrosis

#### Harm outcomes

The safety of the heating procedure will be recorded first by the participant as they conduct the procedure at home and second by the surgical team on the day of surgery. Information on adverse events will continue to be collected by means of spontaneous reports from patients. Attribution of the adverse event to the intervention will be made by participant and clinical opinion.

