#### Analysis of harm outcomes

The frequency of adverse events and the number of patients experiencing events will be tabulated by seriousness and relation to heating protocol (i.e. as adverse reaction (AR), serious adverse event (SAE) or serious adverse reaction (SAR)) and by treatment arm. Non-serious adverse events unrelated to the heating protocol (AE) are recorded in the medical notes only. All ARs, SAEs and SARs will be listed individual by intensity and treatment arm.

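### Blinding of surgeons and necrosis assessors is not secured as written, because heating-related harms are recorded and attributed by clinical staff who are not kept apart from those roles

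*Protocol article*

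**What the plan says.** Methods/design gives the label and its scope: "PREHEAT is a randomised two-arm single-blind parallel group controlled trial of local heat preconditioning", and "Surgeons and assessors evaluating necrosis outcome will be blind to treatment allocation". Randomisation and blinding says that the online system is used "to ensure concealment of treatment allocation for clinicians who are assessing participants" and repeats that "Surgeons and outcome assessors will be blind to treatment allocation".

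Harm outcomes assigns the safety tasks. The participant records the safety of heating at home; it is then recorded "second by the surgical team on the day of surgery". Spontaneous patient reports continue afterwards, and "Attribution of the adverse event to the intervention will be made by participant and clinical opinion".

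Analysis of harm outcomes makes that attribution a filter. Events are "tabulated by seriousness and relation to heating protocol", and "Non-serious adverse events unrelated to the heating protocol (AE) are recorded in the medical notes only".

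Frequency and duration of follow-up has necrosis monitored after the day of surgery by a clinical team member stated to be blinded. A second clinical team member assesses independently in clinic, and two further blinded raters score depth from photographs. In Table 1, adverse event monitoring on the day before surgery is marked as intervention arm only. On the day of surgery and in follow-up it carries no such mark.

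**The concern.** Heating is given in one arm only. A surgical team asked to record how safe the heating was is invited to find out who heated, yet surgeons are declared blind. Attribution opens a second route. The participant is not blind, so when she ascribes an event to the hot water bottle she discloses her arm to whoever forms the clinical opinion. Adverse event monitoring runs through follow-up, the same period in which necrosis is rated, and both bedside raters come from the clinical team.

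What is at stake is the primary objective. Necrosis yes/no is a clinical judgement, and depth and area are reported as the primary clinical assessor scored them. The resulting arm-specific data also feed the sample-size criterion of the performance matrix (Table 3). There is a cost in the other direction too. If clinicians stay fully blind, a non-serious heat reaction could be judged unrelated, stay in the medical notes and be left out of the harms tables.

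**Working it through.** The point rests on comparing the sections, not on a calculation.

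**Side by side**

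| Task | Who does it | Blinding stated | Separated from other roles? |
|---|---|---|---|
| Operating | Surgeons | Blind (Methods/design; Randomisation and blinding) | No statement |
| Recording safety of heating, day of surgery | Surgical team (Harm outcomes) | None specific to this task | No statement |
| Attributing events to heating | Participant and clinical opinion (Harm outcomes) | Participant knows her arm; clinician's role not named | No statement |
| Rating necrosis, ward and clinic | Clinical team member (follow-up section) | Blinded | No statement |
| Second rating in clinic | Another clinical team member (follow-up section) | Covered by the general statement on assessors | Independent of the first rater only |
| Photographic depth rating | Two further raters (follow-up section) | Blinded | Yes, distinct raters |

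**Step 1, surgeons.** A surgical team ordinarily includes the surgeon, and the text does not exclude her or him from recording the safety of heating. Rows 1 and 2 therefore conflict directly unless the check is worded so that it reveals nothing about allocation. Table 1 is compatible with such a check, since the day-of-surgery entry covers both arms, but Harm outcomes describes the task as the safety of heating.

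**Step 2, assessors.** Rows 3 to 5 draw on clinical staff. The document neither says that those who attribute harms also rate necrosis nor says that they do not. This is an unclosed route.

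**Step 3, which outcomes are exposed.** Photographic raters provide a separate reading of presence and depth. They do not measure area, and the arm-specific tables of depth and area use the primary clinical assessor.

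**Context: the plan's own figures.** Inputs from Sample size and recruitment: 180 participants allocated 1:1, taken as 90 per arm; control rate 30%; difference 15 points, hence 15% with heating.

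- Half-width for the difference: 1.96 × √(0.30×0.70/90 + 0.15×0.85/90) = 0.120. The stated ±12 points is reproduced.
- Expected events: 90×0.30 + 90×0.15 = 27 + 13.5 = 40.5, against about 40 stated.

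**Illustration only, on an assumption that the document does not supply.** Suppose that knowing the arm changed *k* borderline yes/no calls out of 90 in the heat arm, in either direction. The heat-arm rate becomes q = (13.5 − k)/90. The size per arm against 30%, with two-sided 5% and 80% power (also an assumption), is

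n = [1.96√(2p̄(1−p̄)) + 0.842√(0.30×0.70 + q(1−q))]² / (0.30 − q)², where p̄ = (0.30 + q)/2.

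| k | q | n per arm |
|---|---|---|
| 3 fewer events | 10.5/90 = 11.7% | 76 |
| 1 fewer | 12.5/90 = 13.9% | 103 |
| 0 | 15.0% | 121 |
| 1 more | 14.5/90 = 16.1% | 144 |
| 3 more | 16.5/90 = 18.3% | 211 |

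This shows that the yes/no entry in the matrix is sensitive to a few calls. It does not show that any call would change.

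**The case against.** A reader might infer that the two sets of statements are incompatible and that the single-blind claim fails. The document does not support that, for several reasons.

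- Redness, blistering or a burn can be recorded without knowing the arm, and relatedness can be judged conditionally, as compatible with heat or not. Table 1 lists day-of-surgery and follow-up monitoring for both arms, so the check need not disclose allocation.
- Nothing says that the surgical team is told the allocation, that it makes the attribution, or that it rates necrosis. The assessor on the ward and in clinic is expressly described as blinded.
- The participant knows her arm, records safety first and shares in the attribution, so the harms data do not depend on blind staff alone. Serious events are tabulated whatever their relation to heating; only non-serious ones are exposed.
- Blinded photographic rating, with kappas against the primary clinical assessor, is already planned.
- This is a condensed article, and form-level detail may sit in the full protocol.

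Most of this stands and limits the point. It does not remove it. The article itself assigns the safety recording to a team that ordinarily includes people it declares blind, and it makes attribution a joint act with an unblinded participant. That is a conflict in what is stated, not a detail left out. The photographic safeguard does not extend to area or supply the main arm-specific tables.

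**Conclusion.** The concern holds in limited form: blinding is not secured as written. The conflict is direct for surgeons. For necrosis assessors there is an open route, with no evidence in the document that anyone used it. It would be wrong to conclude that assessors are unblinded or that the trial is not single-blind.

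The size of any bias cannot be derived from the document. The range of 76 to 211 per arm rests wholly on an assumed change of up to three calls in either direction and is not an estimate of what unblinding would do. The conclusion assumes only that the surgical team includes the surgeons and that those giving clinical opinion may overlap with the clinical team rating necrosis. A statement from the sponsor that the roles were separate would settle the second point. The change is worth making because it is cheap and protects a judgement-based outcome that will shape the definitive trial.

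**What to change.** Reconcile Methods/design, Randomisation and blinding, Harm outcomes, and Frequency and duration of follow-up as follows.

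(a) Describe the day-of-surgery check as a breast-skin check on an allocation-neutral form, completed identically in both arms, in line with Table 1.

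(b) Have relatedness to heating assigned by existing trial staff who already know the allocation and who neither operate nor rate necrosis, using the participant's report. Replace the references to the surgical team and to clinical opinion accordingly.

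(c) Report any known unblinding of surgeons or assessors. Present the planned kappas between the primary clinical assessor and each photographic assessor separately by arm, as a descriptive check. With about 13.5 events expected in the heat arm these will be imprecise, and low agreement could reflect photograph quality as well as unblinding.

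The Discussion gives recruitment as completed on 7 March 2017, with database lock and extraction scheduled for November 2017. For patients already treated, only (c) and a plain statement of who recorded and attributed harms can be applied. Items (a) and (b) carry forward to the definitive trial. The cost is a wording change, one task moved between existing staff, and a by-arm split of agreement tables from data already collected.

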### Frequency and duration of follow-up

The schedule of trial enrolment, interventions and assessments are presented in Table 1. Following the day of surgery monitoring for necrosis will take place on the ward as an inpatient and in outpatient clinics by a member of the clinical team blinded to intervention arm. The follow-up ends at 30–40 days post operation. To establish the reliability of the necrosis outcomes, a second individual from the clinical team will independently assess necrosis in clinic. Photographs will be taken so the necrosis depth can be assessed by two further blinded independent raters.

**Table 1 Tab1:** Schedule of enrolment, interventions and assessments for PREHEAT

	Study period				
	First clinic appointment with reconstructive surgical team	Pre-assessment for surgery	Day before surgery—treatment period	Day of surgery	Follow-up
Action	Day 14	Day 7	Day 1	Day 0	Days 0–30
Eligibility screen	X				
Patient information	X				
Informed consent		X			
Randomisation		X			
Equipment given to patient		X*			
Baseline and pre-operative assessment/variables collected (see Table 2)		X			
Heat preconditioning procedure			X*		
Surgery				X	
Operative assessment/variables collected (see Table 2)				X	
Monitoring for skin necrosis and other post-operative outcomes (see Table 2)					X†
AE monitoring			X*	X	X

*For patients randomised to intervention only

†Skin necrosis measurements are taken at the first outpatient appointment (usually 7 days after discharge so approximately day 12–16) then at every outpatient visit following this until day 30–40

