#### Analysis of primary outcome

As the anticipated number of events (necrosis yes/no) is expected to be relatively few (approximately 40 events in total: 30% control; 15% in intervention), the unadjusted proportion of participants with skin necrosis within 30 days in each trial arm with corresponding 95% CI will initially be calculated. Results will then be tabulated by treatment group for minimisation variables, smoking (yes/no), diabetic (yes/no), autologous- or implant-based reconstruction (yes/no), BRCA carrier status (yes/no).

For necrosis depth (SKIN score), we will present the unadjusted proportions of patients within each category by treatment arm, as assessed by the primary clinical assessor at time of first occurrence (or assessment if none throughout). For patients with necrosis, we will present measures of central tendencies (mean and median) and variability (standard deviation (SD) and interquartile range (IQR)) for necrosis area (3), measured in mm^2^, by treatment arm as assessed by the primary clinical assessor at time of first occurrence. Area will be reported overall (sum of areas by depth) and separately by depth grading.

Necrosis depth (SKIN score) and area measurements will be plotted over time for each individual by treatment group. We will examine the area assessments over time with a view to considering the area under the curve (AUC) as an additional summary estimate. For each patient, we will also determine the maximum depth and area as assessed by the primary assessor over the follow-up period and present the unadjusted proportions of patients within each category. For maximum necrosis area, we will present mean, median, SD and IQR by treatment arm. The proportion of patients for whom the necrosis has been resolved/fully healed within the 30 days will be presented by treatment arm with 95% CI.

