#### Analysis of secondary outcomes

Table 4 summarises the proposed analyses for the secondary outcomes. Additional post-operative outcomes assessed within the 30 follow-up period listed in Table 2 will be summarised by treatment group using suitable measures of central tendencies and variability for continuous data and frequencies and proportions for categorical data. No significance testing will be undertaken.

**Table 4 Tab4:** Analysis of secondary outcomes

Secondary outcome	Analysis
Recruitment rate per month	We will present recruitment numbers by month and compute the average monthly recruitment figure.
Proportion of patients followed-up at 30 days	We will present the overall proportion of patients followed-up at 30 days and the proportion of patients followed-up at 30 days by treatment arm.
Compliance and adherence with heating protocol	We will present the frequency and proportion of patients complying with the allocated intervention as not adhering, one session, two sessions or fully adhering. We will present reasons for non-adherence where available. For each of the three heating sessions, we will present measures of central tendencies (mean and median) and variability (SD and IQR) for the time of occurrence of the heating application, the temperature of the water and duration of the heat supplication.
Length of stay in hospital following SSM/NSM (days)	Kaplan–Meier curves will be plotted by treatment arm for length of stay in hospital, where length of stay is defined as the difference in days between the date the patient was discharged from hospital, and the date they were admitted. A Cox proportional hazards model will be fitted to estimate the intervention effect on length of stay, adjusting for the minimisation variables. Adjusted time to event curves will be plotted. If the proportional hazard assumption is not deemed a reasonable assumption then an alternative method for adjusting the curve will be sought either through use of a different time-to-event model or stratification of the Kaplan–Meier curves [24, 25].
Proportion of patients with necrosis requiring surgical intervention	The proportion of patients with necrosis requiring surgical intervention will be estimated by treatment arm with 95% CI. The surgical intervention required will be summarised using frequencies and proportions by treatment arm.

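### Length of stay is labelled as post-surgical but counted from admission, and the necrosis measures use windows and measurement starts that do not agree with each other

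*Protocol article*

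**What the plan says.** **Length of stay.** The row in Table 4 (Analysis of secondary outcomes) is titled "Length of stay in hospital following SSM/NSM (days"), but the definition in that row is "the difference in days between the date the patient was discharged from hospital, and the date they were admitted". It is analysed with Kaplan–Meier curves and a Cox model adjusted for the minimisation variables. The Intervention section states: "Participants in the intervention arm will be given a hot water bottle and an underwater thermometer for use at home". Heating takes place 12 hours before surgery, on the previous evening. The article gives no admission day for either arm.

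**Window.** Table 1 sets surgery at day 0 and heads the follow-up column days 0–30. Its footnote runs measurements to day 30–40, and the text of the same section says "The follow-up ends at 30–40 days post operation". Under Analysis of primary outcome, yes/no necrosis is counted within 30 days, and so is healing: "The proportion of patients for whom the necrosis has been resolved/fully healed within the 30 days". Maximum depth and area are taken over the whole follow-up period. Retention in Table 4 is at 30 days.

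**Start of measurement.** The Table 1 footnote reads "Skin necrosis measurements are taken at the first outpatient appointment (usually 7 days after discharge so approximately day" 12–16). The Primary outcome section instead has area gridded on the day necrosis occurs, and the follow-up text includes monitoring on the ward. Depth and area are first summarised by arm "as assessed by the primary clinical assessor at time of first occurrence".

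**The concern.** Length of stay is the one secondary outcome with a comparative model, and it tests something heat is hoped to change. Counting from admission adds any pre-operative night to the outcome. That night is not recovery time, and the intervention itself gives one arm a reason to be at home for it.

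The primary objective is to choose between three ways of measuring necrosis. The performance matrix (Table 3) compares them partly on the sample size each would need. If one candidate is cut at day 30 and another is not, part of the difference between them comes from the window and not from the measure.

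First-occurrence depth and area are wound-age dependent. If the first measurement is tied to discharge, and discharge differs by arm, the arms are compared at different days since surgery.

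**Working it through.** **1. The plan's own figures.** Inputs from Sample size and recruitment: 180 participants, 1:1, so 90 per arm; 30% necrosis in controls; a difference of 15 points.
- Control half-width: 1.96 × √(0.30 × 0.70 / 90) = 9.5 points (stated ±9).
- Difference: 1.96 × √(0.21/90 + 0.1275/90) = 12.0 points (stated ±12).
- Events: 90 × 0.30 + 90 × 0.15 = 40.5 (stated about 40).

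All three agree to rounding. The rates are assumed inputs, so these figures do not depend on the rules below.

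**2. Length of stay.** Stay as computed = days from surgery to discharge + days from admission to surgery. Suppose heated patients are admitted on the day of surgery and a share *f* of controls one day earlier. Then mean control stay rises by *f* × 1 day for reasons unrelated to recovery. The share *f* is not in the article, so the whole range is shown. The hazard ratios are simulated with no true effect, mean stay 8 days, an assumed SD of 2 or 3 days, 5,000 per arm and Efron ties.

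| *f* (assumed) | Shift in mean (days) | Discharge hazard ratio, SD 2 | SD 3 |
|---|---|---|---|
| 0 | 0 | 1.00 | 0.98 |
| 25% | 0.25 | 1.12 | 1.10 |
| 50% | 0.5 | 1.22 | 1.16 |
| 100% | 1 | 1.52 | 1.37 |

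The 0.98 in the null row shows the simulation noise. Counted from surgery, the shift is zero for every *f*.

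**3. Window.** The rules side by side:

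| Quantity | Window as written |
|---|---|
| Necrosis yes/no | within 30 days |
| Healing | within 30 days |
| Retention | at 30 days |
| Maximum depth and area | whole follow-up, which ends at day 30–40 |

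Take a wound first seen on day 35. It is outside the yes/no definition but can supply that patient's maximum depth and area. Healing first recorded on day 35 is outside the healing definition, although the wound may have closed before day 30.

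The number of such patients cannot be derived. As an illustration, let a share *q* of the 40.5 events be first seen on days 31–40, equally in both arms. Sample size per arm uses the pooled-variance two-proportion formula, two-sided 5%, 80% power: n = [1.96√(2p̄(1−p̄)) + 0.842√(p₁(1−p₁) + p₂(1−p₂))]² / (p₁−p₂)².

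| *q* (assumed) | Events lost | Rates | n per arm |
|---|---|---|---|
| 0 | 0 | 30% vs 15% | 121 |
| 5% | 2.0 | 28.5% vs 14.25% | 129 |
| 10% | 4.1 | 27% vs 13.5% | 138 |
| 20% | 8.1 | 24% vs 12% | 160 |

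Table 3 gives the point to the measure with the lower sample size, so a narrower window can count against yes/no necrosis alone.

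**4. Start of measurement.** Day 12–16 minus 7 implies discharge on day 5–9. The Background reports for the phase 1 study "an average length of stay from 8 to 4 days". Adding 7 gives first clinic visits at day 15 and day 11; day 11 lies outside the footnote's own range. This 4-day gap arises only if stay really differs that much and measurement really starts in clinic. The rule of measuring on the day of occurrence says otherwise.

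**The case against.** The strongest reply is that the trial does have a surgical clock. Table 1 puts surgery at day 0, the end of follow-up is counted from the operation, and the footnote translates the first visit onto that scale. Seven days after discharge describes when clinics are booked and is not an analysis origin. This stands: only length of stay is actually computed from another date.

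Second, necrosis is watched on the ward, area is to be recorded on the day it occurs, and maxima and individual plots over time are already planned without a day-30 cut. This stands too, and it limits the third part to a conflict needing reconciliation. It does not remove that conflict, because the footnote places the measurements at outpatient visits and the second assessor rates in clinic.

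Third, surgeons are blind, so they could not set admission by arm, and if everyone is admitted on the day of surgery the admission rule is harmless. That is fair. However, blinding of surgeons does not decide where patients spend the evening before. The heating protocol places one arm at home, and the row's title contradicts its definition in any case.

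Fourth, a fixed 30-day window is defensible, applies equally to both arms, and a patient seen on day 35 has clearly been retained to day 30. The fixed window would be a reasonable choice if applied to every measure. As written, it is applied to some and not to others.

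Finally, this is a feasibility trial with mainly descriptive analysis. That limits the consequences, but choosing between the measures is its primary objective.

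**Conclusion.** Two rules are inconsistent as written: length of stay against its own title, and the 30-day window for yes/no necrosis and healing against the whole-follow-up window for the maxima. A third pair, area on the day of occurrence and measurement from the first clinic visit, must be reconciled.

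The possible distortion of stay is 0 to 1 day in the mean, resting on an assumed 0–100% of controls admitted the day before and heated patients on the day. How many findings fall on days 31–40 is unknown. The article does not say whether first-occurrence or maximum values enter Table 3, so the windows there may differ; it is not certain that they do.

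A reader might infer more than this, and the article does not support it:
- That all outcome clocks ignore surgery: they do not.
- That final-visit findings are generally lost: only yes/no necrosis and healing first recorded after day 30 are affected.
- That the arms will be measured 4 days apart, or healing observed for 19 against 15 days (30 − 11 and 30 − 15): the stays come from a non-randomised study of 50 patients, and a 30-day window from surgery is the same length in both arms.
- That stay will be biased by 12.5% (1 day of 8): this needs every control admitted a day early.

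The wording should be corrected before unblinded data are extracted.

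**What to change.** 1. Define length of stay as discharge date minus surgery date, which is what the title says.
2. Use one window, counted from surgery through the final visit at day 30–40, for necrosis yes/no, depth, area, healing and retention, and align the follow-up column of Table 1 with it. State that all columns of Table 3 use this window.
3. Reconcile the day-of-occurrence rule for area with the footnote that starts measurements at the first outpatient visit. Report first-occurrence depth and area with day since surgery, alongside the maxima already planned.

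Cost: changes of wording in the analysis plan, with no new visit or assessment. Admission and discharge dates are needed for the current definition, and the day of surgery is the schedule's day 0, so the dates should be on file; that is an inference, since the article does not list them as fields. The real downsides are that 30-day labels become end of follow-up (day 30–40) and that patients' windows differ by up to 10 days. Reporting the day of the final visit by arm would show whether that matters.
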